### Interventions

#### Explanation for the choice of comparators {6b}

Usual care (control arm) is no SMS vaccine reminder but might include other non-SMS reminders like telephone or written reminders. Most parents receive a letter from the Australian Government’s universal healthcare payer, Medicare, including a notice if childcare subsidy payments are at risk due to missed vaccinations. Parents in the usual care arm will not receive an SMS reminder for upcoming vaccination, but they may receive an appointment confirmation reminder via SMS if they have already scheduled an appointment where such confirmations are used routinely by the clinic.

#### Intervention description {11a}

SmartVax software interrogates various proprietary electronic clinic information systems to identify children registered with the practice who are age-eligible for a routine childhood vaccine dose. After confirming that the child is either < 2 months old (due for their first vaccine dose) or has received at least one prior vaccine dose at the clinic, the system automates the sending of a personalised SMS reminder to the parent from the clinic. AuTOMATIC will investigate 12 combinations of SMS reminders under a factorial design comprising four message framings and three message timings.

The framing of the SMS reminders will be either (1) framed neutrally, i.e. merely factual with no mention of a benefit or risk; (2) framed positively, i.e. associating vaccination with a direct personal benefit; (3) framed in terms of potential risk, i.e. associating late or missed vaccination with a direct personal health risk; or (4) framed in terms of social importance, i.e. associating vaccination with a broader societal value or benefit.

The timing of the SMS reminders will be either (1) 14 days before the scheduled vaccination due date, (2) on the scheduled due date, or (3) 7 days after the scheduled due date of vaccination if a vaccine has not been received.

If the child is recorded in the clinic information system as vaccinated before the scheduled timing of the SMS reminder delivery, then no message will be sent. The text content of each of the SMS framing and timing options is provided in the *supplementary material*.

#### Criteria for discontinuing or modifying allocated interventions {11b}

A study arm may be discontinued after a scheduled analysis according to the pre-specified rules described below; parents assigned to an active arm which is discontinued will be re-assigned to usual care (no SMS).

#### Relevant concomitant care permitted or prohibited during the trial {11d}

All parents will continue to receive whatever constitutes usual care from their clinic as previously described in {6b}. Any additional pre-emptive SMS reminders for routine childhood vaccination will not be permitted for the duration of the study.

#### Provisions for post-trial care {30}

There is no post-trial care required for participating parents; however, extended use of the trial SMS reminder system will continue for a short period of time after the trial for clinics to adjust to their previous usual care program.

### Participant timeline {13}

#### Eligibility assessment and enrolment (21–28 days prior to due date)

The time schedule of events has been designed to allow digital automation (Fig. 2). The SmartVax software will interrogate the clinic electronic practice information system each day to identify any child who is due for a routine scheduled 2, 4, 6, 12, and 18 month or 4 year old vaccine dose in 21–28 days’ time. The software then checks that the child is associated with a parent in the practice information system, that the parent has a valid mobile phone number and that the child is < 2 months old or has had at least one prior vaccine dose received at the clinic.

**Fig. 2 Fig2:**
[figure not shown]
Schedule of enrolment, interventions and assessments for the AuTOMATIC study

For each child, the SmartVax software will assign, using a specified algorithm across all participating sites, a unique study identifier based on a scrambling of the child’s date of birth, their first initial and their surname. The parent of the child will also be assigned a unique study identifier based on a scrambling of their mobile phone number. The scrambling algorithm will ensure that parents registered across multiple sites or with multiple children will receive the same randomisation intervention arm as previously assigned and thereby prevent them from being assigned to multiple discordant arms. The scrambling algorithm will generate a deterministic, non-reversible identifier from the input data elements.

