### Objectives {7} and outcomes {12}

#### Primary objective

The primary objective is to determine whether, compared to usual practice, a personalised SMS reminder with specific timing and message framing, will improve the rate of timely vaccination in primary care, that is, the proportion of children vaccinated within 28 days of the scheduled date for a routine childhood vaccine dose.

A child and their siblings may receive more than one scheduled vaccination during the follow-up period; the parent will be the unit of randomisation and will only be randomised once. The parent whose behaviour we seek to change can only be considered naïve to the intervention on the first child-vaccination occasion; therefore, the primary analysis will be performed on the outcome of the first child-vaccination occasion for each parent after randomisation (the *index vaccine occasion* and the *index child*).

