#### Randomisation (21–28 days prior to due date)

The SmartVax software will perform an encrypted randomisation request by sending the unique child and parent identifier, the child’s date of birth, the practice identifier and the vaccine scheduled due date to a trial middleware application hosted on a server at the Telethon Kids Institute. The trial middleware application will check if the parent has previously received an arm allocation and if the child and/or parent has been excluded from enrolment.

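### The parent identifier rests on the mobile number alone, so the same arm is assured only while the number stays the same; a new number can lead to a second randomisation linked to the same child

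*Protocol article*

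**What the plan says.** Under Participant timeline {13}, in the text following Fig. 2, the article describes two identifiers.

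- **Child:** "a unique study identifier based on a scrambling of the child’s date of birth, their first initial and their surname".
- **Parent:** "The parent of the child will also be assigned a unique study identifier based on a scrambling of their mobile phone number".

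It then makes a guarantee: "The scrambling algorithm will ensure that parents registered across multiple sites or with multiple children will receive the same randomisation intervention arm as previously assigned". The purpose given is to "prevent them from being assigned to multiple discordant arms". On the algorithm itself it says: "The scrambling algorithm will generate a deterministic, non-reversible identifier from the input data elements".

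The Randomisation section says the request is made by "sending the unique child and parent identifier, the child’s date of birth, the practice identifier and the vaccine scheduled due date" to the trial middleware. The look-up is then described: "The trial middleware application will check if the parent has previously received an arm allocation". In that sentence the child is named only for the exclusion check.

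The Primary objective section sets the rule that all this serves: "the parent will be the unit of randomisation and will only be randomised once". It restricts the primary analysis to the first occasion per parent because only then is the parent naive to the intervention.

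**The concern.** A deterministic scramble of a phone number identifies a number, not a person or a family. If the number on a later record differs, the parent identifier differs too, and the look-up as described finds no earlier allocation. The family can then enter as a new parent.

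Three things would be at stake:

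- The family may be put in a second, usually different, arm.
- The same child may supply a second index occasion, which need not be naive. If two clinics hold different numbers for one child at the same time, one dose could count under two arms.
- The primary model terms listed under Statistical methods {20a} are intervention, vaccine age, clinic and calendar time. No family or child term is among them, so a repeat would be treated as an independent parent.

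Secondary outcomes cover all doses and all children, so a discordant later arm would affect those as well.

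**Working it through.** **Step 1: the logic of the key.** The article gives no figure to reproduce on this point.

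- Same number, any site, any sibling: same parent identifier, earlier arm found. The guarantee holds.
- Number changed between two due doses: new parent identifier, same child identifier. The parent look-up finds nothing, and no child look-up for an earlier allocation is described. A second randomisation is possible.
- Other parent's number recorded at another clinic: same result.
- Exclusion criterion (3) does not catch these cases. It removes identifier data that are recorded incorrectly, whereas a new or second number is a correct entry.

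**Step 2: chance that a second draw is discordant.** Inputs, from Sequence generation {16a}: 1/5 for usual care and 1/15 for each of 12 active arms (check: 1/5 + 12/15 = 1). For two independent draws at these ratios:

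- P(same arm) = (1/5)² + 12 × (1/15)² = 0.0400 + 0.0533 = 0.0933
- P(different arm) = 1 − 0.0933 = 0.907
- of which usual care and an active arm, in either order: 2 × 0.2 × 0.8 = 0.320
- and two different active arms: 0.8² − 0.0533 = 0.587

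These values belong to the initial ratios. If both draws came after allocation had concentrated, the figure would be lower. As an illustrative extreme, with 20% usual care and 80% in a single active arm at both draws, P(different) = 1 − (0.04 + 0.64) = 0.32.

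**Step 3: how many repeats could be non-naive.** Usual care sends no SMS, so a family first allocated to it has had no trial message. At the initial ratios at most 1 − 1/5 = 80% of repeats could be non-naive. The true share is smaller, because no message is sent when the child is vaccinated before the send date.

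**Step 4: illustrative counts.** The share of repeats is not in the document; 1% to 5% of 10,000 is an assumption. Both right-hand columns use the initial ratios throughout.

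| Assumed share | Repeats | Discordant (× 0.907) | Non-naive, at most (× 0.80) |
|---|---|---|---|
| 1% | 100 | 91 | 80 |
| 3% | 300 | 272 | 240 |
| 5% | 500 | 453 | 400 |

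**The case against.** The strongest reply has four parts.

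- **The child identifier may already be used.** It reaches the middleware in the same request, and the article neither says nor rules out that it links records. This stands against any statement that a new number *will* cause a second randomisation; only *can* is supported. It does not rescue the guarantee, which the article rests on the scrambling algorithm and a look-up described for the parent.
- **Matching rules are operational detail left to the full protocol or analysis plan.** True of many details. Here, though, the article itself makes a firm claim and describes a mechanism that does not deliver it.
- **The guarantee speaks of parents at several sites or with several children, not of changed numbers or a second parent.** Partly right. The other parent is a different person, so the once-only rule for parents is not literally broken in that case, although the child is then tied to two arms. But different sites can hold different numbers for the same parent, and that is within the claim.
- **Exposure is limited.** A repeat needs a new number and a further due dose while enrolment is open (expected to end in December 2023). A second clinic generally needs a prior dose there, except for infants under 2 months. This limits the frequency but does not make it zero.

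A reader might also take the Trial status figures, 5462 parents randomised and 5370 index cases, a gap of 92, as a sign of duplication. They do not show it; the gap may have other causes.

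**Conclusion.** The point holds as a limited one. The claim to ensure one arm is true only for records sharing a mobile number. Followed as written, the procedure can randomise a family again under a different valid number and create a second index occasion for the same child, contrary to the aim set out under Primary objective.

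Its size is unknown. The 0.907 rests on two independent draws at the initial ratios, the 80% is a ceiling at those ratios, and the counts depend on an assumed share of repeats. It would be tempting to infer that hundreds of index outcomes are contaminated, or that error rates or power are materially affected. The article supports neither: it gives no rate of number changes, and no effect on bias or operating characteristics has been shown. This is a minor weakness that is cheap to remove.

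**What to change.** 1. In the Randomisation section, check for an earlier allocation on the child identifier as well as the parent identifier. If either matches, return the earliest allocated arm, also where the two identifiers match different arms, and create no new index occasion.
2. In the primary analysis, keep only the first index occasion per child identifier. This can be applied to parents already randomised.
3. In the text following Fig. 2, limit the guarantee to records that share a mobile number or a child identifier. A new number presented with a new sibling matches on neither and would still be missed.

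**Cost:** one further look-up on an identifier already sent, and a de-duplication step. There will be rare false matches of different children with the same birth date, first initial and surname; twins and multiple births, the obvious source, are already excluded. A few repeat enrolments would no longer count towards the 10,000.

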#### Randomisation (21–28 days prior to due date)

The SmartVax software will perform an encrypted randomisation request by sending the unique child and parent identifier, the child’s date of birth, the practice identifier and the vaccine scheduled due date to a trial middleware application hosted on a server at the Telethon Kids Institute. The trial middleware application will check if the parent has previously received an arm allocation and if the child and/or parent has been excluded from enrolment.

#### Intervention delivery

Parents will receive an automated SMS reminder at a time and with a message framing in accordance with their assigned arm.

#### Recording of vaccine receipt (vaccine due date followed up to 28 days later)

Each day, the SmartVax system will identify which children have received a vaccine as recorded in the clinic software system; this data will be uploaded to the trial middleware system and subsequently to the study database.

#### Sample size {14}

At least 1500 parents (when the first interim analysis is scheduled to occur) and no more than 10,000 parents will be enrolled unless one or more of the pre-specified stopping rule(s) is/are met at a scheduled analysis.

The maximum sample size was selected on the basis of trial feasibility and, due to the adaptive nature of the trial, the usefulness of sample size was evaluated via simulation which was used to assess the trials operating characteristics.

Under the planned decision thresholds (the “Interim analyses {21b}” section), we estimated a probability of approximately 0.06 of incorrectly declaring any active arm *superior* when all were equivalent to usual care and a probability of less than 0.02 of incorrectly declaring a specific active arm *effective* when equivalent to usual care. We estimated a probability of approximately 0.87 for declaring an active arm effective when it improved the odds of 28-day vaccination by a factor of 1.4 over all other interventions.

Further details of the trial simulations are provided in the *supplementary material*.

#### Recruitment {15}

We will maximise involvement of eligible clinics for this study through an established network that is already associated with SmartVax under its existing adverse event monitoring program and Primary Health Networks (coordination centres for healthcare services within community regions). At the time of protocol publication, SmartVax adverse event monitoring is used by over 600 clinics across Australia.

### Assignment of interventions: allocation

#### Sequence generation {16a}, concealment mechanism {16b} and implementation {16c}

The parent is the unit of randomisation and their allocation will be automatically generated by the middleware application on a daily basis. A randomisation sequence is digitally pre-generated and stored within the middleware application; the next assignment is taken from this ordered list as each new eligible parent is enrolled. The randomisation sequence is generated using a mass-weighted urn design [15] to allow for incorporation of the non-integer target allocation weights generated from the response adaptive randomisation procedure.

At trial initiation, the allocation probability is 1/5 for usual care and 1/15 for each of the 12 active intervention arms. The allocation of 1/5 to the usual care arm will remain fixed throughout the trial unless dropped according to a pre-specified decision rule.

After each scheduled analysis, the probability of allocation to each active intervention arm will be updated such that it is proportional to the scaled posterior probability that the arm is best among all active arms with respect to the primary outcome. In this manner, better performing active arms will receive progressively higher weighting of allocations than worse performing active arms. If an active arm is performing significantly worse than the usual care arm, then that arm will be discontinued (the probability of allocation to the arm will be set to zero), and those parents will be manually switched to usual care, and subsequent outcome data will be excluded from analyses.

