#### Interim analyses {21b}

Regular analyses will be conducted throughout the trial. The first analysis will be scheduled to occur after 1500 index children have been followed to 28 days after the scheduled date for their index vaccine. After that first analysis, future analyses will be scheduled to occur after every additional 500 index children have been followed to 28 days after the scheduled due date for their index vaccine. These analyses will include all data on all index vaccination occasions which are at least 28 days past their scheduled due date.

At each analysis, the model parameter’s posterior distribution will be used to assess trial decision rules and to update the target allocation probabilities for each active arm. At each analysis, we will calculate the posterior probability that (i) each active arm is *effective* compared to usual care, that is, it increases the log-odds of vaccination relative to usual care, (ii) each active arm is *superior* to all other active arms, that is, it increases the log-odds of vaccination more than all other interventions, and (iii) an active arm is, on average (equally-weighted across all interventions), effective compared to usual care.

Based on these calculated probabilities, a decision will be made after each analysis whether to (i) discontinue an active arm for *lack of effectiveness* if there is a small (low) probability that it increases the proportion vaccinated by 28 days compared to usual care only; (ii) discontinue the usual care arm if, compared to usual care, all active arms collectively on average, or any particular active arm, has/have high probability of increasing the proportion vaccinated by 28 days; (iii) discontinue the trial for *futility* if all active arms have been discontinued for lack of effectiveness; and (iv) discontinue the trial for *success* if any active arm has high posterior probability of being the best overall, and usual care has been discontinued.

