The probability thresholds for discontinuing are scaled according to the current sample size relative to the maximum sample size and have been chosen based on extensive simulations to achieve good trial-wise frequentist operating characteristics. Denoting by *n*_*t*_ the sample size at the *t*th scheduled analysis, for effectiveness, the threshold is 1 – 0.01(*n*_*t*_*/10,000)*^*0.5*^; for ineffectiveness, the threshold is 0.01(*n*_*t*_*/10,000)*^*0.5*^; and for superiority, the threshold is 0.95–0.25 (*n*_*t*_*/10,000)*^*0.5*^. Following the analysis, the target allocation probabilities to each continuing active arm will be updated to be proportional to the variance and sample-size scaled probability that each arm is superior.

If after 10,000 parents have been randomised and none of the above trial stopping rules have been met, no further parents will be randomised, and posterior summaries of model parameters and comparisons of interest will be calculated.

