#### Methods in analysis to handle protocol non-adherence and any statistical methods to handle missing data {20c}

Where digital errors may occur, for example, a clinic server malfunction leading to no SMS being sent as assigned, participants will be included in each scheduled analyses according to their intended assignment. As this is equally likely to occur in any of the active arms, there is no significant risk of bias. The data capture system is designed to ensure all fields are populated so missing data is not expected; however, in the event any data is missing, we will not use imputation in our analyses.

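### The data rule for a discontinued arm conflicts with the definition of the analysis set and, read literally, discards index outcomes of parents whose reminder date had already passed

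*Protocol article*

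**What the plan says.** Four places in the protocol article bear on this.

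- **Sequence generation {16a}, concealment mechanism {16b} and implementation {16c}.** When an active arm is discontinued, "those parents will be manually switched to usual care, and subsequent outcome data will be excluded from analyses". No exception is written. Criteria for discontinuing {11b} repeats the re-assignment but gives no data rule.
- **Interim analyses {21b}.** On the data set of each scheduled analysis: "These analyses will include all data on all index vaccination occasions which are at least 28 days past their scheduled due date". Discontinued arms are not excepted.
- **Primary objective.** The parent is randomised once, and "the primary analysis will be performed on the outcome of the first child-vaccination occasion for each parent after randomisation".
- **Methods to handle non-adherence and missing data {20c}.** For digital errors, such as a message not sent because of a server fault, "participants will be included in each scheduled analyses according to their intended assignment".

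**The concern.** Parents are randomised 21-28 days before the due date, are reminded at day -14, 0 or +7, and reach the endpoint at day +28. When an arm is discontinued while enrolment continues, some of its parents will have passed their reminder date without yet having a mature index outcome. They were handled as assigned, and a later switch to no SMS cannot undo a reminder already sent. Their index outcomes are valid under the assigned arm.

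Read literally, the allocation section drops these outcomes, while the interim-analysis section keeps them. The literal exclusion is a post-randomisation exclusion in one arm, triggered by that arm's poor results. If the arm fell below the boundary by chance, the discarded outcomes would on average move its estimate back towards the truth. At stake are the reported effect of a discontinued message and, if discontinued arms stay in it, the equally weighted average effect in Interim analyses {21b}, which can close usual care.

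**Working it through.** No figure in the article describes this rule, so there is none to reproduce. The check has four steps.

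**1. Who is caught.** Randomisation to endpoint takes 21 + 28 = 49 to 28 + 28 = 56 days. Reminder to endpoint takes 42, 28 or 21 days for the three timings. With even entry, the share of in-flight parents already past their reminder date is:

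- day -14: 42/56 to 42/49 = 75-86%
- day 0: 28/56 to 28/49 = 50-57%
- day +7: 21/56 to 21/49 = 38-43%

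**2. Drop boundary at the first analysis (n = 1500).**

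- Initial allocation ("the allocation probability is 1/5 for usual care and 1/15 for each of the 12 active intervention arms") gives about 300 in usual care and 100 per active arm.
- The article expects 80% vaccinated by day 28, so the usual-care odds are 4.
- The ineffectiveness threshold is 0.01 × (1500/10,000)^0.5 = 0.0039, or z = -2.66.
- At an observed arm rate of 66.8%, OR = (0.668/0.332)/4 = 0.503, so log OR = -0.687.
- SE = √[1/(300 × 0.16) + 1/(100 × 0.668 × 0.332)] = 0.257, so z = -2.68, just past the boundary.

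**3. Effect of keeping parents past their reminder date.** The number in flight is not stated, so a range is assumed.

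- *Low value, 92.* Trial status gives 5462 randomised and 5370 index cases. The difference is 92, but the article does not say that these are the in-flight parents.
- *High value, about 500.* If 10,000 were reached by December 2023 from 1500 in August 2021, accrual would be 8500/28 = 304 a month, or about 490-560 over 49-56 days. This takes the maximum sample size as reached and subtracts matured from randomised parents, so it is rough.

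At 1/15 per arm these totals give 6.1 and 33.3 parents. With m of them retained at a true rate of 80%, the arm's expected rate is (66.8 + 0.8m)/(100 + m). Usual care is held at 80%.

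| In flight (total) | Timing | m retained | OR |
|---|---|---|---|
| 92 | day -14 | 4.6-5.3 | 0.52 |
| 92 | day 0 | 3.1-3.5 | 0.51 |
| 92 | day +7 | 2.3-2.6 | 0.51 |
| 500 | day -14 | 25.0-28.6 | 0.57-0.58 |
| 500 | day 0 | 16.7-19.0 | 0.55 |
| 500 | day +7 | 12.5-14.3 | 0.54 |

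Counting all 33.3 in-flight parents would give 0.59, but that includes parents whose reminder date had not come.

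**4. Effect at trial end.** A simplified simulation used 13 arms, 80% throughout, analyses from 1500 to 10,000 by 500, the article's thresholds, a normal approximation, an assumed form of adaptive allocation and no clinic, age or calendar terms. In 2000 runs with all arms equal, about 4.6% of active arms were dropped. Their mean OR (averaged on the log scale) was 0.59 at the drop and 0.63 at trial end with the arm's own data fixed. Adding in-flight outcomes gave:

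| In flight (total) | End-of-trial OR | Gain over 0.633 |
|---|---|---|
| 92 | 0.636 | 0.003 |
| 250 | 0.642 | 0.010 |
| 500 | 0.650 | 0.018 |
| 1000 | 0.664 | 0.031 |

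These gains are upper bounds, because every in-flight parent was counted as past the reminder date. The simulation does not match the article's operating characteristics (0.92 against 0.87 for declaring an arm with OR 1.4 effective; 0.03 against 0.06 for a false declaration of superiority). The supplement with the simulation details is not shown, so these results indicate scale only.

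**The case against.** The strongest reply is that the allocation section does not say that outcomes of already reminded parents are dropped. Coming straight after the switch, the exclusion can be read as covering only later occasions, when the parent no longer gets the assigned message; excluding those is understandable. The interim-analysis section supports that reading, and the SAP, which is not shown, may settle it. This stands against any claim that the trial certainly discards these outcomes. It does not remove the conflict: the exclusion is written without a limit, and the two sections give different answers for the same index outcomes.

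Four further inferences are tempting but unsupported:

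- *The estimate is frozen.* Only the arm's own data are fixed. Usual-care data keep updating the contrast, as the move from 0.59 to 0.63 shows.
- *The exclusion causes the low estimate.* Most of it comes from selection at the boundary and from ending allocation, which is a planned feature. Keeping all in-flight data still leaves 0.64-0.66 against a truth of 1.
- *A dropped arm is a chance low.* An arm with a true OR of 0.7 was dropped in about 60% of 1000 simulated runs.
- *The intended-assignment statement in {20c} decides the matter.* It is written for digital errors and supports the principle only by analogy.

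The effect on the equally weighted average is also small. Moving one of 12 arms from 0.503 to 0.576 changes the mean log OR by ln(0.576/0.503)/12 = 0.011. A value that is too low makes closing usual care harder, not easier.

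Finally, the proposed rule also excludes some randomised index parents. That is true, but its cut-off is a scheduled date set by due date and arm, which does not depend on the outcome.

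**Conclusion.** The point holds as a conflict between two stated rules, with a modest consequence. For index outcomes that mature after an arm is discontinued, the allocation section and the interim-analysis section cannot both be followed. Under the literal exclusion, valid outcomes are lost from an arm chosen for its low result; if that result was chance, the lost data would on average have pulled the estimate back.

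For a null arm just at the boundary at n = 1500, the OR would move from about 0.50 to 0.51-0.58. At trial end the gain is below 0.01 with 92 in flight, about 0.02 with 500 and about 0.03 with 1000. These sizes rest on an assumed backlog, even entry, a true rate of 80% in both arms and, for trial end, an uncalibrated simulation that overstates the gain. They do not support a reading that the rule seriously distorts the trial's conclusions. The change is still worth making, because the literal rule gives a worse estimate than the alternative and the correction is cheap.

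**What to change.** Reconcile the allocation section with Interim analyses {21b} in one sentence, for example: *when an active arm is discontinued, occasions whose scheduled reminder date falls after the date of the switch are excluded; every index occasion whose scheduled reminder date fell before the switch stays in the primary analysis under the assigned arm, whether or not a message was sent.*

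The last clause matters. No message goes to a child already recorded as vaccinated, so keeping only occasions with a message sent would select on the outcome, most of all in the day +7 arms.

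The cost is one sentence in the protocol and, if the SAP does not already contain it, in the SAP. The scheduled reminder date is already captured (Plans for assessment and collection of outcomes {18a}). The date of each switch must be on record. The switch itself and the rest of trial conduct stay as they are.
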